## Abstract

**Background:**

Acute myocardial infarction (AMI) remains the leading cause of mortality worldwide. The majority of patients who suffer an AMI have a history of at least one of the standard modifiable risk factors (SMuRFs): smoking, hypertension, dyslipidemia, and diabetes mellitus. However, emerging scientific evidence recognizes a clinically significant and increasing proportion of patients presenting with AMI without any SMuRF (SMuRF-less patients). To date, there are no adequate data to define specific risk factors or biomarkers associated with the development of AMIs in these patients.

**Methods:**

The ‘‘Beyond-SMuRFs Study’’ is a prospective, non-interventional cohort trial designed to enroll patients with AMI and no previous coronary intervention history, who undergo coronary angiography in two academic hospitals in Thessaloniki, Greece. The rationale of the study is to investigate potential relations between SMuRF-less AMIs and the clinical, laboratory and imaging profile of patients, by comparing parameters between patients with and without SMuRFs. Complete demographic and comprehensive clinical data will be recorded, Venous blood samples will be collected before coronary angiography and the following parameters will be measured: total blood count, standard biochemistry parameters, coagulation tests, hormone levels, glycosylated hemoglobin, N- terminal pro-B-type natriuretic peptide and high-sensitivity troponin T levels- as well as serum levels of novel atherosclerosis indicators and pro-inflammatory biomarkers. Furthermore, all participants will undergo a complete and comprehensive transthoracic echocardiographic assessment according to a pre-specified protocol within 24 h from admission. Among others, 2D-speckle-tracking echocardiographic analysis of cardiac chambers and non-invasive calculation of myocardial work indices for the left ventricle will be performed. Moreover, all patients will be assessed for angiographic parameters and the complexity of coronary artery disease using the SYNTAX score. Multivariable linear and logistic regression models will be used to phenotypically characterize SMuRF-less patients and investigate independent clinical, laboratory, echocardiographic and angiographic biomarkers-predictors of SMuRF-less status in AMI.The first patient was enrolled in March 2022 and completion of enrollment is expected until December 2023.

**Discussion:**

The ‘‘Beyond-SmuRFs’’ study is an ongoing prospective trial aiming to investigate potential clinical, laboratory and imaging biomarkers associated with the occurrence of AMIs in SMuRF-less patients. The configuration of these patients’ profiles could lead to the development of personalized risk-stratification models predicting the occurrence of cardiovascular events in SΜuRF-less individuals.

**Trial Registration:**

ClinicalTrials.gov Identifier: NCT05535582 / September 10, 2022.

## Background

Acute myocardial infarction (AMI) remains the leading cause of mortality worldwide [1]. The incidence of coronary artery disease (CAD) and -its most adverse manifestation- AMI, has been proven to rise along with the increasing prevalence of major cardiovascular risk factors, such as obesity, smoking, and hypercholesterolemia [2]. These comorbidities have been well recognized as risk factors of coronary artery disease (CAD) and are often used to evaluate the risk of sustaining an acute coronary event, including AMI. Furthermore, the primary and secondary prevention of AMIs has primarily focused on the modification and treatment of standard modifiable risk factors (SMuRFs), namely smoking, diabetes mellitus, dyslipidaemia, and hypertension [2]. However, recent registries indicate a growing population of patients suffering an acute coronary syndrome (ACS) without any SMuRF (SMuRF-less patients) [3–6]. Over the past decade, the prevalence of such cases among patients presenting with ST-segment elevation myocardial infarction (STEMI) has increased from 13 to 27% in a large, national registry [3].

To date, scientific evidence on the pathogenesis and etiology of SMuRF-less AMI remains limited, although it constitutes an increasingly recognized clinical entity. A popular hypothesis implicates systematic inflammation and high levels of intra-coronary pro-inflammatory cytokines, but data are scarce. Pro-inflammatory and atherosclerosis biomarkers, such as lipoprotein (a) [Lp(a)], C-reactive protein and fibrinogen, have been shown to have higher specificity in predicting worse prognosis of AMI in SMuRF-less patients, as compared to patients with SMuRFs, but no studies have been conducted to investigate their role as predictors of SMuRF-less AMIs [4, 7]. Furthermore, large observational studies have indicated several demographic features potentially linked to SMuRF-less status in AMI, but the results are contradictory, probably due to marked heterogeneity in studied populations [8–10]. Hence, pinpointing sensitive clinical and laboratory parameters, as well as diagnostic approaches, for the prediction of AMI in patients without SMuRFs is crucial, as it concerns an increasing proportion of patients with CAD, who are rather under-represented in registries and clinical trials of cardiovascular risk-assessment [11].

The aim of this study is, therefore, to investigate potential clinical and/or laboratory characteristics associated with SMuRF-less AMIs by comparing the prevalence of clinical parameters and levels of laboratory and imaging indicators among patients with and without SMuRFs. The ultimate goal is the development of a predictive risk stratification model capable of recognizing patients without SMuRFs at high risk for AMI. Secondarily, the study aims at investigating differences in the prognosis of SMuRF-less patients compared to those with SMuRFs.

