## Methods

### Study design and population

The ‘‘Beyond-SMuRFs Study’’ (ClinicalTrials.gov Identifier: NCT05535582) is an investigator-initiated, prospective, non-interventional cohort trial involving patients suffering from AMI and undergoing coronary angiography. The study is performed in accordance with the general principles outlined in the Declaration of Helsinki [12] and the rules of good clinical practice (GCP), and has been approved by the Ethics Committee of the Aristotle University of Thessaloniki (reference number: 136945/2022).

A total of 500 consecutive patients presenting with STEMI or Non-STEMI (NSTEMI) at two academic hospitals in Thessaloniki, Greece, undergoing primary or emergency coronary angiography, will be enrolled in the study. All eligible participants will provide informed written consent before enrollment. Patients with a history of previous AMI or previous coronary intervention, either percutaneous or surgical, will be excluded, as the calculation of the SYNTAX score for these patients is not possible. Detailed eligibility criteria are described in ​Table 1.

**Table 1 Tab1:** Inclusion and exclusion criteria of the study population

Inclusion Criteria	Exclusion Criteria
• Age > 18 years • Hospitalization for acute myocardial infarction (AMI) with or without ST elevation (based on the Fourth Universal Definition of Myocardial Infarction) within the previous 4 weeks • Coronary angiography before or after hospitalization for AMI, in which at least one stenosis > 50% in a major epicardial coronary artery (left anterior descending artery, left circumflex artery, right coronary artery) or a branch thereof with a diameter of at least 2 mm was observed.	• Inability or refusal to provide informed consent • Age > 80 years • History of hospitalization due to AMI prior to the present AMI • History of coronary revascularization prior to the present AMI • Previous coronary angiography (prior to the present AMI) showing > 50% stenosis in a major epicardial coronary artery

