Patients will be divided into two groups based on their medical history: (i) Group A: SMuRF-less patients, (ii) Group B: Patients with SMuRFs, defined as those who fulfilled at least one of the following criteria: (i) known history of hypertension and/or antihypertensive treatment prior to AMI, (ii) self-reported use of tobacco products on a systematic basis for up to 12 months before AMI, (iii) history of diabetes mellitus type 1 or 2 and/or treatment with antidiabetic tablets or insulin before AMI or diagnosis of diabetes mellitus based on HbA1c during AMI hospitalization, (iv) known hypercholesterolemia (total cholesterol > 200 mg/dl / LDLc > 150 mg/dl) or treatment with statins or PCSK9is, before AMI. SMuRF-less patients (Group A) are defined as those suffering an AMI in the absence of these comorbidities.

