### Statistical analysis

Clinical parametersc laboratory findings and imaging indices of interest will be compared among patients with and without SMuRFs to phenotypically characterize the SMuRF-less group, and identify any particular associations of these biomarkers with the SMuRF-less status. Subsequently, univariate logistic regression analysis will be performed to identify independent predictors of SMuRF-less AMIs. A multivariate logistic regression model will be constructed by forcing univariably significant and clinically relevant variables into the multivariable model. The G*Power software was utilized by a specialist statistician in order to calculate the sample size required to derive statistical significance. It was estimated that to detect an odds ratio > 2 with a prevalence of 15% of SMuRF-less status among AMIs, approximately 75 SMuRF-less patients will be required (with a probability for Type I error: 0.80, and statistical significance level: 0.05). Therefore, 500 patients (with and without SMuRFs) will be included in the present study. An odds ratio > 2 will be interpreted as a prediction of a 2-fold higher probability of having SMuRF-less AMI than an AMI attributed to SMuRFs.

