Baseline patient characteristics of each group will be examined and compared using the chi-square test for categorical variables and the 2-sided Student’s t-test for continuous variables or non-parametric tests (Wilcoxon, Mann-Whitney U etc.), when assumptions of normality are not met. Categorical variables will be represented by frequencies and percentages (%) and continuous variables will be summarized by mean ± standard deviation (SD) or median (1st -3rd quartile), as appropriate. In terms of statistical tests recruited for outcomes calculation, the two groups of patients will be compared to each other to identify clinical, laboratory and imaging biomarkers associated with a higher or lower probability of developing a SMuRF-less AMI. The chi-square test will be used to compare the prevalence of clinical parameters among patients with and without SMuRFs, and the t-test and Mann-Whitney U test will be utilized to compare the mean levels of laboratory and imaging biomarkers between the two groups. As mentioned before, univariate linear and logistic regression analyses will be applied to calculate univariate odds ratios, and then multivariate regression analyses will be performed. Finally, in order to identify the optimal combination of epidemiological, clinical, laboratory and imaging biomarkers associated with SMuRF-less AMIs, supervised machine learning algorithms will be used. The resulting clinical-laboratory prediction models will be evaluated with Receiver Operating Characteristic (ROC) curves.

A time-to-event analysis will be performed to assess whether the absence of SMuRFs is associated with better or worse clinical prognosis of patients (secondary outcome). Event rates will be compared by the long-rank test. Μultivariable Cox proportional hazard models will be utilized to adjust the results for clinically relevant and univariately significant variables. The 2-tailed p value of 0.05 will be considered the significance threshold for all statistical tests. All outcomes will be reported with 95% confidence intervals. Data management and statistical analyses will be conducted using SPSS software, version 26 (IBM SPSS Statistics) and R version 3.4.4 (R Foundation for Statistical Computing, Vienna, Austria).

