## Discussion

‘’Beyond-SMuRF’’ is a prospective cohort trial, enrolling recently hospitalized patients with AMI and aspiring to identify clinical, laboratory and imaging biomarkers associated with SMuRF-less status. So far, suggested polygenic clinical risk-score models seem to underestimate the risk in SMuRF-less patients and are usually incapable of identifying cardiovascular risk factors on top of SMuRFs [18]. Therefore, the rationale of this study is -by comparing clinical, laboratory, echocardiographic and angiographic parameters between the SMuRF-less group and the group of patients with SMuRFs- to assess novel biomarkers as predictors of SMuRF-less AMIs and ultimately generate a risk-stratification tool for this increasingly recognized entity. To our knowledge, this is the first study to comprehensively attempt an in-depth, multiparametric evaluation of the profile of SMuRF-less population with AMI. Although several studies have reported clinical outcomes in SMuRF-less patients, there is a lack of evidence regarding clinical, laboratory and imaging findings in these patients.

Several studies have reported baseline demographic characteristics among patients with and without SMuRFs [3, 11, 18, 19]. Ηowever, no marked differences have been explored so far between the two groups in terms of basic demographic features such as age and sex. Moreover, differences in baseline clinical characteristics and comorbidities have not been thoroughly evaluated on a systematic basis, which adds to the novelty of this study. For instance, rheumatic and autoimmune diseases, as well as abdominal obesity, alcohol consumption and drug use, have been associated with increased cardiovascular risk but have never been assessed as potential absolute explainers of SMuRF-less AMIs [18, 20]. Furthermore, mental health status and psychosocial risk factors have been linked to CAD, but data regarding the association thereof with SMuRF-less status in AMI are lacking [20–24]. Additionally, the lack of physical activity, as well as specific socioeconomic parameters, have been proven drivers of CAD, but never evaluated in the context of SMuRF-less AMIs [24–26].

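### Every participant has an AMI, so the models describe who is SMuRF-less among AMI patients; they cannot support the wording about developing a SMuRF-less AMI or the risk-model goal

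*Protocol article*

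**What the plan says.** **Goal.** The Background first sets an aim of association, to be met by comparing patients with and without SMuRFs. It then adds: "The ultimate goal is the development of a predictive risk stratification model capable of recognizing patients without SMuRFs at high risk for AMI". The Discussion repeats this as an intention to "ultimately generate a risk-stratification tool for this increasingly recognized entity". The Abstract's discussion and the closing paragraph under Limitations say, conditionally, that such profiling could lead to risk models.

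**Population.** Study design and population describes a "prospective, non-interventional cohort trial involving patients suffering from AMI and undergoing coronary angiography". Table 1 requires "Hospitalization for acute myocardial infarction (AMI) with or without ST elevation" and at least one stenosis above 50%, and it excludes earlier AMI hospitalisation and earlier revascularisation. The comparison group of interest is also made up of cases: "SMuRF-less patients (Group A) are defined as those suffering an AMI in the absence of these comorbidities".

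**Models.** Under Statistical analysis, "univariate logistic regression analysis will be performed to identify independent predictors of SMuRF-less AMIs", followed by a multivariable model. Then, "in order to identify the optimal combination of epidemiological, clinical, laboratory and imaging biomarkers associated with SMuRF-less AMIs, supervised machine learning algorithms will be used", with the resulting prediction models judged by ROC curves.

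**Interpretation.** The same section says the comparison of the two groups will identify "biomarkers associated with a higher or lower probability of developing a SMuRF-less AMI". In the sample-size paragraph, however, the odds ratio is read as SMuRF-less AMI against AMI attributed to SMuRFs.

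**The concern.** A model that recognises people without SMuRFs at high risk of AMI has to estimate the probability of AMI given no SMuRFs and the predictors. The planned models estimate something else: the probability of having no SMuRFs given an AMI and the predictors. One cannot be turned into the other without data on SMuRF-less people who have not had an AMI, or outside incidence data, and the article describes neither. Follow-up does not help, because it counts death and MACE after the index AMI.

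What is at stake is how the results are read. A marker that is rarer in SMuRF-less than in SMuRF patients could be taken as lowering the chance of a SMuRF-less AMI when it only tends to accompany SMuRFs. A score built this way would rank AMI-free people by how little they resemble SMuRF patients, not by their risk. The Discussion comes close to this step when it takes lower body-mass index and triglycerides in the SMuRF-less group of a registry analysis as a hint that these factors may not drive atherosclerosis.

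**Working it through.** **The plan's own figure.** 75 SMuRF-less patients at 15% prevalence gives 75 / 0.15 = 500. This reproduces, but it has no bearing here: the number of AMI-free SMuRF-less participants is 0 whatever the total.

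**Inputs.** The articles's design supplies the two groups, both AMI cases, and the target odds ratio of 2. It gives no factor prevalence in the source populations and no relative risk for AMI. The values below are therefore assumptions, varied to show a range.

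**Formula.** Let q be the prevalence of a factor in a source population and RR its relative risk for AMI there. Among AMI cases from that population, the odds of having the factor are RR × q / (1 − q). The odds ratio from the planned logistic model, before adjustment, is then

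OR = [RR(SMuRF-less) × q(SMuRF-less) / (1 − q(SMuRF-less))] ÷ [RR(SMuRF) × q(SMuRF) / (1 − q(SMuRF))].

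If the two relative risks are equal they cancel, and the OR shows only how the factor is distributed between SMuRF-less and SMuRF people.

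**Worked case.** RR 2 in both groups, prevalence 15% and 30%:
- SMuRF-less cases: 2 × 0.15 / 0.85 = 0.353
- SMuRF cases: 2 × 0.30 / 0.70 = 0.857
- OR = 0.353 / 0.857 = 0.41

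**Range of scenarios (all assumed).**

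| RR, SMuRF-less | RR, SMuRF | Prevalence, SMuRF-less | Prevalence, SMuRF | OR among AMI cases | If misread as AMI risk in SMuRF-less people |
|---|---|---|---|---|---|
| 2 | 2 | 30% | 30% | 1.0 | effect missed |
| 2 | 2 | 15% | 30% | 0.41 | effect reversed |
| 2 | 4 | 30% | 30% | 0.5 | effect reversed |
| 1 | 1 | 30% | 17.65% | 2.0 | effect invented |
| 1 | 0.5 | 30% | 30% | 2.0 | effect invented |
| 3 | 1.5 | 30% | 30% | 2.0 | direction right, size wrong |
| 4 | 2 | 30% | 30% | 2.0 | direction right, size wrong |

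The last four rows all give the odds ratio of 2 that the study is sized to detect, while the relative risk in SMuRF-less people is 1, 1, 3 and 4. The data cannot tell these situations apart.

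**Read as the plan's case-case contrast,** every OR in the table is a correct description of how the factor differs between the two kinds of AMI patient.

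**The case against.** The strongest reply is that the operative objective is one the design can answer. The Background calls the risk model an ultimate goal. The primary outcome, under Data collection and study procedures, is association with SMuRF-less status in AMI. The Discussion names association as the main objective and leaves predictive value to later, larger trials. The sample-size paragraph sets one AMI group against the other, which is the right comparator. On that reading an OR of 0.41 is simply true: the factor is less common among SMuRF-less AMIs.

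Most of this stands. It means that two stronger readings, which a reader might infer, are not supported. The first is that the plan's main conclusion has the wrong sign. That would follow only if the OR were reread as AMI risk, and the plan's own rule for reading the OR does not do so. The second is that the article offers a larger AMI-only study as the remedy. It speaks of larger trials without saying whom they would enrol.

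What the reply does not reach is the wording under Statistical analysis on developing a SMuRF-less AMI, which belongs to the analysis of these data and not to a later programme. Nor does it reach the Discussion's intention to generate a risk tool. The Discussion's caveat is about imaging changes that may follow the AMI and about further testing. The Limitations mention the observational nature, the Greek population, the age limit and the restricted set of biomarkers, but not the absence of AMI-free people.

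**Conclusion.** The point holds as a mismatch between some of the claims and the data. The planned models estimate the odds of being SMuRF-less among patients with a first AMI and obstructive coronary disease. They cannot give the probability of developing a SMuRF-less AMI, nor a model of AMI risk in people without SMuRFs, and a larger sample of the same kind would not change that. This conclusion rests on the enrolment criteria alone.

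The figures from 0.41 to 2.0 rest on assumed prevalences and relative risks. They show that a misreading can miss, reverse or invent an effect; they do not show how likely or how large this would be for any marker in the study. The within-AMI comparison and the prognosis analysis are unaffected.

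**What to change.** 1. In the Background, Statistical analysis and Discussion, state the estimand as the odds of being SMuRF-less among patients with a first AMI and obstructive coronary disease.
2. Under Statistical analysis, replace the phrase on the probability of developing a SMuRF-less AMI with wording to that effect.
3. Describe the machine-learning output, and its ROC curve, as a classifier of SMuRF-less status among AMI patients.
4. In the Background and Discussion, withdraw the claim that these data will yield a model or tool for AMI risk. Bring the conditional statements in the Abstract's discussion and at the end of the Limitations section into line.
5. Add to the Limitations that a model of AMI risk needs a comparator of SMuRF-less people without AMI, which this study does not have.

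This needs no change to enrolment, sample size, measurements or follow-up. The cost is a narrower claim.

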## Methods

### Study design and population

The ‘‘Beyond-SMuRFs Study’’ (ClinicalTrials.gov Identifier: NCT05535582) is an investigator-initiated, prospective, non-interventional cohort trial involving patients suffering from AMI and undergoing coronary angiography. The study is performed in accordance with the general principles outlined in the Declaration of Helsinki [12] and the rules of good clinical practice (GCP), and has been approved by the Ethics Committee of the Aristotle University of Thessaloniki (reference number: 136945/2022).

A total of 500 consecutive patients presenting with STEMI or Non-STEMI (NSTEMI) at two academic hospitals in Thessaloniki, Greece, undergoing primary or emergency coronary angiography, will be enrolled in the study. All eligible participants will provide informed written consent before enrollment. Patients with a history of previous AMI or previous coronary intervention, either percutaneous or surgical, will be excluded, as the calculation of the SYNTAX score for these patients is not possible. Detailed eligibility criteria are described in ​Table 1.

**Table 1 Tab1:** Inclusion and exclusion criteria of the study population

Inclusion Criteria	Exclusion Criteria
• Age > 18 years • Hospitalization for acute myocardial infarction (AMI) with or without ST elevation (based on the Fourth Universal Definition of Myocardial Infarction) within the previous 4 weeks • Coronary angiography before or after hospitalization for AMI, in which at least one stenosis > 50% in a major epicardial coronary artery (left anterior descending artery, left circumflex artery, right coronary artery) or a branch thereof with a diameter of at least 2 mm was observed.	• Inability or refusal to provide informed consent • Age > 80 years • History of hospitalization due to AMI prior to the present AMI • History of coronary revascularization prior to the present AMI • Previous coronary angiography (prior to the present AMI) showing > 50% stenosis in a major epicardial coronary artery

Patients will be divided into two groups based on their medical history: (i) Group A: SMuRF-less patients, (ii) Group B: Patients with SMuRFs, defined as those who fulfilled at least one of the following criteria: (i) known history of hypertension and/or antihypertensive treatment prior to AMI, (ii) self-reported use of tobacco products on a systematic basis for up to 12 months before AMI, (iii) history of diabetes mellitus type 1 or 2 and/or treatment with antidiabetic tablets or insulin before AMI or diagnosis of diabetes mellitus based on HbA1c during AMI hospitalization, (iv) known hypercholesterolemia (total cholesterol > 200 mg/dl / LDLc > 150 mg/dl) or treatment with statins or PCSK9is, before AMI. SMuRF-less patients (Group A) are defined as those suffering an AMI in the absence of these comorbidities.

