A complete and comprehensive transthoracic echocardiographic assessment (TTE) will be performed within 24 hours from admission. All TTE studies will be conducted by certified sonographers/cardiologists using high-end scanners (e.g. Vivid E95, GE Healthcare, Chicago, IL, USA). All analyses will be separately performed by two dedicated expert cardiologists, blinded to the clinical data of all participants. All cardiac chamber sizing quantification, two-dimensional (2-D) and Doppler measurements will be performed in accordance with current recommendations [14, 15]. Simpson’s biplane method will be employed for the calculation of left ventricular ejection fraction (LVEF) for the left ventricle (LV) and abnormal values of conventional LV diastolic parameters will be determined based on recently published criteria [15]. LV diastolic function parameters include mitral inflow and annular velocities and the derived trans-mitral to averaged septal and lateral annular early diastolic velocity ratio (E/e’). All right ventricular (RV) systolic function parameters including tricuspid annular plane systolic excursion (TAPSE), fractional area change (FAC), systolic movement of the RV lateral wall using tissue Doppler imaging (S’), pulmonary artery systolic pressure (PASP) will be evaluated as per current guidelines [16].

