Two-dimensional (2D) speckle tracking echocardiography will be employed to calculate strain measurements for the LV, left atrium (LA), and RV. Global longitudinal strain (GLS) will be derived from the calculation of the average of the peak systolic longitudinal strain of all segments for each chamber. To estimate myocardial work indices, LV GLS and peak systolic LV pressure measurements will be integrated to the aforementioned module [17]. Four different indices of myocardial work will be calculated including (i) LV global work index (LVGWI, mmHg %), representing the total work within the LV pressure-strain loops, (ii) LV global constructive work (LVGCW, mmHg %), defined as the work performed during myocardial shortening in systole and the work during myocardial lengthening in isovolumic relaxation, (iii) LV global wasted work (LVGWW, mmHg %), representing the work contributing to the lengthening of the cardiac myocytes during systole and the shortening during isovolumic relaxation, and (iv) LV global work efficiency (LVGWE, %), defining the percentage of effectively spend work by the LV myocytes and obtained by the following formula: (LVGCW/[LVGCW + LVGWW]) × 100%.

The primary outcome of the study is to compare clinical, laboratory and imaging parameters among SMuRF-less patients and patients with SMuRFs, thereby exploring clinical, laboratory, echocardiographic and angiographic biomarkers potentially associated with SMuRF-less status in AMI. Subsequently, we aim to assess these parameters as potential independent predictors of SMuRF-less AMIs (logistic regression analysis). Secondary goals include a comparison of short- and long-term mortality and major adverse cardiovascular events (MACE), as well as of the complexity and severity of CAD, between AMI patients with and without history of SMuRFs (Fig. 1). Short-term outcomes include all-cause death and MACE during hospitalization and/or 30 days after hospital admission. Patients will also be followed-up for a median period of 24 months after enrollment to evaluate long-term prognosis. All deaths will be ascertained by searching in the Greek web-based national health insurance system. Apart from death, MACE will be documented by independent physicians either through hospital reports or via in-person or telephonic interviews. The first patient was enrolled in April 2022 and completion of enrolment is expected until August 2023.

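### Table 1's four-week entry window contradicts the admission-based schedule; anyone enrolled late under it would lack on-schedule research samples and echo, and would have survived to entry by design

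*Protocol article*

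**What the plan says.** The protocol article gives two pictures of when a patient enters the cohort.

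**Entry after the acute phase is allowed.** Table 1 (Study design and population) includes patients hospitalised for AMI "based on the Fourth Universal Definition of Myocardial Infarction) within the previous 4 weeks". Its angiographic criterion reads "Coronary angiography before or after hospitalization for AMI". The Discussion likewise describes the cohort as patients with a recent hospitalisation for AMI.

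**Entry at presentation is assumed.**
- Study design and population: "A total of 500 consecutive patients presenting with STEMI or Non-STEMI (NSTEMI) at two academic hospitals in Thessaloniki, Greece", undergoing primary or emergency angiography. Written consent comes before enrolment.
- Abstract, Methods: "Venous blood samples will be collected before coronary angiography".
- Data collection and study procedures: clinical characteristics are recorded after consent. IL-6, suPAR, Lp(a) and the apolipoproteins are measured on admission, and the physical activity questionnaire is completed before discharge. The echocardiogram "will be performed within 24 hours from admission".
- Same section, outcomes: "Short-term outcomes include all-cause death and MACE during hospitalization and/or 30 days after hospital admission". For the long term: "Patients will also be followed-up for a median period of 24 months after enrollment".

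Table 1 also excludes patients with "Previous coronary angiography (prior to the present AMI) showing > 50% stenosis in a major epicardial coronary artery", and those unable or unwilling to consent.

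**The concern.** A patient first approached in week three satisfies Table 1 but cannot satisfy the measurement schedule unless the research procedures were done before consent. Those biomarkers and imaging indices are the primary comparison, so a mixture of acute and late values would blur it.

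The second problem is survival. The short-term outcome runs from admission, but a patient enrolled on a later day is known to have lived until then. Deaths between admission and possible enrolment are never counted, so in-hospital and 30-day mortality could come out too low. Prognosis is a secondary aim, and the Discussion cites emerging evidence of a worse course in SMuRF-less patients. If early deaths were lost unevenly between the groups, that contrast would be distorted.

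**Working it through.** The plan states no figure on this point to reproduce. The check compares time windows and then illustrates what late entry could do.

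**1. Windows side by side**

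| Item | Timing in the article | Feasible on schedule after a week-three consent? |
|---|---|---|
| Research blood (IL-6, suPAR, Lp(a), apolipoproteins) | before angiography / on admission | No |
| Protocol echo with strain and myocardial work | within 24 hours of admission | No |
| Physical activity questionnaire | before discharge | Only if still in hospital |
| Routine admission laboratory values, peak troponin, angiographic images | admission / hospital stay | Yes, from hospital records |
| Death and MACE | to 30 days from admission | Only from consent onwards |

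Four weeks is 28 days, and 28/30 = 93% of the short-term window. Enrolment on day 28 leaves 30 − 28 = 2 days at risk.

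**2. Observed 30-day risk among patients enrolled on day d**

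Observed risk = M(1 − F)/(1 − M·F), where M is the true 30-day mortality and F the share of 30-day deaths occurring before day d. The article gives neither quantity. Assume M = 6%, with two death patterns: uniform over 30 days (F = d/30), or front-loaded with a half-time of 3 days.

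| Enrolment day | F, uniform | Observed | F, front-loaded | Observed |
|---|---|---|---|---|
| 0 | 0 | 6.0% | 0 | 6.0% |
| 7 | 0.23 | 4.7% | 0.80 | 1.3% |
| 14 | 0.47 | 3.3% | 0.96 | 0.2% |
| 28 | 0.93 | 0.4% | 1.00 | 0.0% |

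Example, day 7, uniform: 0.06 × 0.767/(1 − 0.06 × 0.233) = 0.0460/0.986 = 4.7%. For M between 3% and 10%, day-7 enrolment gives 2.3–7.9% (uniform) and 0.6–2.2% (front-loaded). These figures apply to patients enrolled on that day. The effect on the whole cohort depends on the unknown mix of enrolment days.

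**3. Effect on the group comparison**

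The formula is the same, with s the share of a group's 30-day deaths that occur before enrolment. Assumed true mortality is 10% in SMuRF-less patients and 7% in the others, so the true risk ratio is 0.10/0.07 = 1.43.

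| s, SMuRF-less | s, others | Observed risks | Risk ratio |
|---|---|---|---|
| 0.25 | 0.25 | 0.0769 / 0.0534 | 1.44 |
| 0.50 | 0.50 | 0.0526 / 0.0363 | 1.45 |
| 0.50 | 0.25 | 0.0526 / 0.0534 | 0.98 |

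With 7% in both groups and the unequal split, 0.0363/0.0534 = 0.68 where the truth is 1. Equal loss barely moves the ratio; unequal loss can remove or reverse it.

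**4. Numbers of events**

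The sample-size paragraph expects about 75 SMuRF-less patients. At an assumed 4–10% mortality that is 3 to 7.5 deaths, so each lost death counts.

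**5. The angiography wording**

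An angiogram after AMI onset but before admission satisfies the inclusion wording and escapes the exclusion. One done before the present AMI and showing more than 50% stenosis in a major epicardial artery satisfies the inclusion's angiographic wording but is excluded. The two criteria overlap badly but do not contradict each other in every case.

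**The case against.** The strongest reply is that every operational statement places enrolment in the index stay: consecutive presenters, emergency angiography, blood beforehand, echo within a day, questionnaire before discharge. Nowhere does the article say that anyone is enrolled in week three. If all patients enter at presentation, the late-entry loss is small and the four-week phrase is only loose wording. This stands as a limit on the claim. It does not remove the contradiction, because the Discussion echoes Table 1 and the eligibility rule is what a site would apply.

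Other objections also stand in part:
- A reader might infer that acute measurements are simply unavailable for late enrollees. That is too broad, since routine laboratory values, peak troponin and angiograms can come from records. Only the research assays and the protocol echo are at risk.
- A reader might take the ratio of 0.98 as evidence that the mortality signal would vanish. It follows from an assumed 50% versus 25% split that nothing in the article supports. The Discussion's remarks on prognosis and delayed reperfusion say nothing about deaths before consent in either group.
- Patients too ill to consent are lost through the consent criterion, not through the four-week window.
- Mortality is a secondary outcome, and survivor selection bears less directly on the primary baseline comparison. Time origin and delayed-entry coding could be settled in an analysis plan that is not shown. That plan could not, however, reconcile the eligibility wording.

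**Conclusion.** The point holds as an internal contradiction: Table 1's entry window and the loose angiography timing do not fit the text above the table or the admission-based schedule. A late enrollee under Table 1 could not have the research blood or protocol echo on schedule after consent and would be a survivor by design, so in-hospital and 30-day death may be understated.

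It is tempting to conclude that early deaths do drop out and that the comparison by SMuRF status is therefore biased. The documents do not support this. The loss is a risk that Table 1 permits, and material bias in the comparison also needs early death or time to consent to differ by group. The size cannot be computed; all mortality figures and risk ratios above are illustrations on stated assumptions. The sample size is unaffected. The correction is worth making because it is cheap and the short-term events will be few.

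**What to change.** 1. Reconcile Table 1 with the text so that enrolment and the qualifying angiogram belong to the index AMI hospitalisation. Clarify the before-or-after wording against the exclusion of angiograms prior to the present AMI. State when consent is taken relative to sampling.
2. Use hospital admission as the single time origin for short- and long-term outcomes.
3. For anyone consented after admission, including patients already enrolled, start time at risk on the consent date (delayed entry) in the log-rank and Cox analyses and in the 30-day estimates. Count only events after that date.
4. Restrict the admission-biomarker and echo comparisons to patients measured on schedule.
5. State as a limitation that patients unable to consent are not recovered by any of this, and report deaths before consent where known.

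The cost is a wording change, two dates per patient (admission and consent) and an entry time in the survival models. A few late enrollees leave some analyses. With so few expected deaths, early risk sets will be small and the earliest part of the delayed-entry curve unstable, so the number at risk should be shown beside it. Enrolment began in spring 2022, so new wording alone does not deal with patients already recruited; steps 3 and 4 do.
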